### Follow-up

The patients will be followed up for at least 10 years after treatment. During follow-up visits, the oncological and toxilogical outcomes will be evaluated during RT; at 1, 2 weeks and 3, 6 months after RT; every 6 months for the first 5 years, and then annually. All recurrences should be confirmed by histology or cytology if possible. Acute radiation toxicity will be graded according to the National Cancer Institute’s Common Terminology Criteria for Adverse Events version 3.0 (CTCAE 3.0). Late radiation toxicity will be graded according to the Radiation Therapy Oncology Group (RTOG)/the European Organization for Research and Treatment of Cancer (EORTC) late radiation morbidity scale, and QoL assessment will be performed according to patient-reported questionnaires (EORTC QLQ-C30 and QLQ-BR23). Table 3 shows the follow-up schedule.

**Table 3 Tab3:** Follow-up workflow

	Pre-RT	During RT		6 months after RT				6 months to 5 years after RT	5–10 years after RT
	baseline	weekly	end	1 week	2 weeks	3 months	6 months	every 6 months	annually
History and physical exam	X	X	X	X	X	X	X	X	X
Complete blood cell count	X	X	X	X	X	X	X	X	X
Thyroid function (Blood analysis)	X					X	X	X	X
†Myocardial enzyme spectrum	X					X	X	X	X
Chest CT	X					X	X	X	X
Regional nodal ultrasonography	X					X	X	X	X
Ultrasonography/CT/MRI for liver	X					X	X	X	X
Twelve-lead electrocardiogram	X					X	X	X	X
Echocardiography	X					X	X	X	X
†‡Coronary CT angiography	X							(1) 3 years	6, 10 years
Quality of life	X		X			X	X	X	

† Applicable to patients for whom the examination is accessible

‡ The frequency of coronary CT angiography examination is dependent on patient age and the baseline status of coronary artery stenosis. For patients younger than 65 years and with less than 50% stenosis in left anterior descending coronary artery (LAD), left circumflex artery (LCX) and right coronary artery (RCA), the coronary CT angiography examination is scheduled at 3, 6, and 10 years after RT. If the stenosis severity in one of the three main coronary arteries exceeds 50% and/or the patient is older than 65 years, the coronary CT angiography examination is scheduled at 1, 3, 6, and 10 years after RT. If the stenosis severity in one of the three main coronary arteries exceeds 75%, revascularization should be performed and the coronary CT angiography examination is scheduled at 3, 6, and 10 years after RT

### Statistical analysis & sample size calculation

The primary end point is DFS. We hypothesize that IMNI group has superior 5-year DFS to the no IMNI group. Based on previous studies, the 5-year DFS rate was 70–74% for patients with node-positive breast cancer who did not receive IMNI [11, 17]. To detect a 6% difference in the 5-year DFS (78% in the IMNI group and 72% in the no IMNI group; equivalent to a Hazard Ratio [HR] of 0.76), with a power of 80%, and a one-sided alpha value of 2.5%, a total of 414 events are required. With an anticipation of recruitment during a 5-year period, the accrual target to randomize is 1800 patients.

Patients will be analyzed according to the intention to treat principle. Two interim analyses for efficacy and futility are planned to occur when 207 DFS events (50% information) and 311 DFS events (75% information) are observed. The critical values for the interim analyses will be determined using the Lan–DeMets implementation of the O’Brien–Fleming boundary for interim efficacy analysis and a linear 20% inefficacy boundary for futility analysis [18]. The principal investigator and the protocol committee will perform the analysis. A Data Monitoring Committee (DMC) will be set up to oversee the trial and to decide whether the trial should be stopped.

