## Methods/design

### Study design

This is an open label, randomized, multi-center phase III trial for which 1800 participants will be randomized (1:1) to an IMNI group (IMNI) or a no IMN irradiation group (no IMNI).

A flow chart giving an overview of the study design is shown in Fig. 1.

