### Trial status

Recruitment started in May 2020 and is currently ongoing.

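### As worded, the protocol has the trial's own leadership carry out the interim efficacy and futility comparisons of an open-label trial, with 50% and then 25% of the primary events still to come

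*Protocol article*

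**What the plan says.** All of the key text is in the protocol article, section Statistical analysis & sample size calculation.

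- Final event target: "a total of 414 events are required".
- Interim looks: "Two interim analyses for efficacy and futility are planned to occur when 207 DFS events (50% information) and 311 DFS events (75% information) are observed". A Lan–DeMets O'Brien–Fleming efficacy boundary and a linear 20% inefficacy boundary for futility follow.
- The next sentence names who does the work: "The principal investigator and the protocol committee will perform the analysis".
- The one after that gives the stopping decision to another body: "A Data Monitoring Committee (DMC) will be set up to oversee the trial and to decide whether the trial should be stopped".

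Under Study design the article adds "This is an open label, randomized, multi-center phase III trial", and under Trial status, "Recruitment started in May 2020 and is currently ongoing". The Follow-up section asks for pathological confirmation of recurrence where it can be obtained. It does not say who decides that a recurrence has occurred.

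The article does not describe the DMC as independent and does not restrict access to interim results.

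**The concern.** Whoever performs an efficacy and futility comparison sees the difference between the arms. If the principal investigator and protocol committee perform it, the DMC's later decision cannot restore confidentiality, because the result started with the people it should be kept from.

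This is a rule that the article states, not a detail left to another document. A DMC charter that gave the interim runs to an independent statistician would conflict with this sentence, so the wording needs attention either way.

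The open-label design makes confidentiality of the aggregate result more important. Staff who know each patient's arm could act on a known trend, for example in how an equivocal finding is worked up. Leadership could be influenced in decisions on the endpoint, the event target or the timing of analyses. The group-sequential boundaries control error on the premise that data collected after a look are not altered by knowledge of it. What is at stake is whether a reader of the final DFS result can rule out operational bias.

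**Working it through.** **Inputs from the article.** 5-year DFS 72% without and 78% with IMNI, HR 0.76, 80% power, one-sided alpha 2.5%, 414 events, looks at 207 and 311 (all from Statistical analysis & sample size calculation). 1,800 patients randomised 1:1 (Study design). 5-year recruitment (Statistical analysis & sample size calculation).

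**1. Reproduce the plan's own figures.**
- Hazard ratio under proportional hazards: ln(0.78)/ln(0.72) = 0.7563, stated as 0.76.
- Schoenfeld events: 4(1.960 + 0.842)² / (ln HR)². HR 0.76 gives 417; the unrounded 0.7563 gives 403. Freedman's formula gives 423 and 408. The stated 414 lies within about 3% of each.
- Power with 414 events at HR 0.76: 79.7%.
- Information fractions: 207/414 = 0.500 and 311/414 = 0.751, as stated.

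The event counts are sound. The point concerns who sees the result, not the arithmetic.

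**2. Events outstanding when a result would be seen.** No assumption is needed.
- After the first look: 414 − 207 = 207, or 50%.
- After the second look: 414 − 311 = 103, or 25%.

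**3. Calendar timing.** Assumptions not stated in the article: uniform accrual over 5 years, exponential DFS at the design rates, no drop-out.
- Hazards: −ln(0.72)/5 = 0.0657 and −ln(0.78)/5 = 0.0497 per year.
- Accrual per arm: 900/5 = 180 per year.
- Expected events per arm at time T, with m = min(T, 5): 180 × [m − (e^(−λ(T−m)) − e^(−λT))/λ].
- At T = 4.67 years: about 116.6 + 90.3, which is about 207.

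| Events | Time (years) | Randomised |
|---|---|---|
| 207 | 4.67 | about 1,681 |
| 311 | 5.85 | 1,800 |
| 414 | 7.10 | 1,800 |

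Unrandomised at the first look: 1,800 − 1,681 = 119, about 120 or 7%. With drop-out of 1–2% per year (also an assumption) the times become 4.71–4.74, 5.92–6.00 and 7.23–7.37 years. The first look still falls shortly before accrual ends.

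**4. Which analysis is meant.** The sentence says analysis in the singular and does not call it interim. It stands after the interim boundaries and before the DMC's stopping role, which points to the interim looks. If it instead means every analysis in the trial, the interim ones are still included.

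**The case against.** The strongest reply has four parts.

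**Ambiguous wording.** The paragraph opens with the intention-to-treat principle, so the sentence may simply allocate responsibility for analysis in general, and a full protocol or charter not shown here may separate out the interim runs. This stands as a limit on certainty. It does not remove the point, because the general reading still covers the interim looks.

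**Other safeguards.** A reader might infer that nothing else protects the remaining data. The article does not support that. The DMC, not the investigators, decides on stopping. Looks are triggered by event counts, against named boundaries and a stated target. Table 3 applies one imaging schedule with no distinction by arm, which limits unequal searching for recurrence. Death from any cause, a DFS component, leaves no room for judgement. These narrow the routes to bias, but none keeps the comparison confidential.

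**Who judges recurrence.** A reader might infer that the leadership or the treating team decides whether recurrence has occurred. The article does not say who does. It also does not set out the protocol committee's membership or powers, so it cannot be assumed to consist of recruiting and treating clinicians.

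**Limited reach.** Under the assumptions above, about 93% of patients are already randomised at the first look and accrual is complete before the second. Radiotherapy lasts 3 or 5 weeks, so most patients will have finished it by then. This stands: changed enrolment or treatment delivery is a minor route.

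**Conclusion.** The point holds in a limited form. Followed as written, the plan has trial leadership produce, and therefore see, the interim between-arm DFS results. That leadership would see them is an inference from their performing the analysis, though a direct one.

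The outstanding events, 207 (50%) and 103 (25%), follow from the article's own figures. The roughly 120 unrandomised patients rest on uniform accrual, exponential DFS and no drop-out. The main exposure is later recurrence work-up and decisions on trial conduct.

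A reader might go further and infer that the type I error is inflated by some amount, or that the final result will be biased. The article supports neither: the size and direction of any operational bias cannot be derived from it, and 414, 207 and 311 need no correction. This is a low-cost improvement to the safeguards, not a flaw that invalidates the design.

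**What to change.** Replace the sentence on who performs the analysis with wording such as:

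> Interim comparative analyses are run by a statistician who is not involved in recruitment, treatment, endpoint assessment or the protocol committee (for example the DMC's statistician), and go only to the DMC. The principal investigator and the protocol committee receive only the DMC's recommendation until the trial stops or 414 events are reached. The principal investigator and the protocol committee carry out the final analysis.

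The DMC charter should say the same.

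**Cost.** A short wording change. Leadership loses sight of interim comparative results, and the interim runs move to a statistician outside the committee. Sample size, event target, boundaries and endpoint are unchanged. It should be settled before the first look, because a comparison once seen cannot be unseen.

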### Radiotherapy quality assurance

According to the guidelines for quality assurance (QA) protocol of individual trials laid down by the US National Cancer Institute Work Group on Radiotherapy Quality Assurance [19], the POTENTIAL trial will formulate a tiered RT QA protocol requirement, including general credentialing, trial specific credentialing, and individual case review. Before opening inclusion, all participating centers will provide the qualified documents of the QA process of the CT simulator, LINAC, and the RT planning system for general credentialing. To ensure quality and uniformity between centers, delineation and treatment planning guidelines are described in detail in the protocol. All participating centers will perform a dry run, focusing on target delineation, RT planning generation, and planning QA on phantoms, to assess compliance with the protocols. During inclusion, central individual case review on the target delineation, RT planning, and treatment position verification data will be performed prospectively for the first 10 patients included at each participating center and an additional 10 patients if major deviation is found in 2 out of the first 10 patients, which then will be performed randomly for 5% of all included patients thereafter.

### Ethics

The study protocol has been approved by the ethics committee of the Cancer Hospital, Chinese Academy of Medical Sciences (19/317–2101). The study is registered in ClinicalTrails.gov (NCT04320979).

### Trial status

Recruitment started in May 2020 and is currently ongoing.

## Discussion

In this report, we present the design of the POTENTIAL trial, which aims to investigate whether IMNI can improve DFS in high-risk breast cancer with pN+ after mastectomy. We also intend to determine which subgroups of patients might derive an OS benefit from IMNI. The results from studies designed to evaluate the effect of IMNI itself were conflicting. Some retrospective studies showed that delivering IMNI could improve DFS significantly compared with not delivering IMNI [20–25], whereas other studies demonstrated no benefit of IMNI on DFS [26–28]. Only a few studies observed that for some subgroups of patients with high-risk factors, such as ypN1 (1–3 positive nodes among all axillary nodes harvested) disease, node-positive disease, inner/central tumor, clinical stage II–III breast cancer before neoadjuvant systemic therapy, there is a trend toward improved OS with IMNI [20, 23–26]. The DBCG-IMN prospective study suggested that IMNI improved 8-year OS from 72.2 to 75.9% (HR = 0.82, *p* = 0.005), and greater OS benefit was seen in subgroups of patients with ≥4 positive nodes, or with 1–3 positive nodes and medial tumors [11]. By contrast, the French randomized study was the only one to evaluate postmastectomy IMNI itself and showed no OS benefit from IMNI in the entire cohort or any subgroup of patients [10]. This failure to demonstrate a survival benefit for IMNI in the French study could be explained as follows. Firstly, low-risk patients, such as patients with pN0–1 disease, accounted for a major proportion of the cohort, thus the overestimation of the risk of IMN involvement probably decreased the power of the study. Another retrospective study included patients after breast-conserving surgery, most of whom had pN0 disease or did not undergo axillary lymph node dissection, and also showed that no benefit could be attributed to IMNI [28]. Secondly, the study intended to detect a 10% difference in OS between the IMNI group and the no IMNI group at 10 years, which might have been too optimistic. Moreover, quality control of RT was not planned and deviations from the protocol might have compromised the effect of IMNI; RT was performed in the 2-dimensional era, thus the IMN area could have been partially irradiated in some patients in the IMNI group, and protection of the heart could not be performed routinely. Lastly, the systemic therapy used was weak compared with current practice.

In our study, we will evaluate IMNI in high-risk patients who were treated with modern systemic therapy and 3D RT techniques. The risk of IMN involvement is associated significantly with the axillary lymph node burden. The incidence of IMN involvement was 4.4, 18.8, and 58.2% for patients with 0, 1–3 and ≥ 4 positive axillary lymph nodes [5]. Considering that most of the patients with pN0 disease do not have indications to receive PMRT, we will only include patients with pN+ disease. With regard to patients with T1–2 disease and 1–3 positive axillary lymph nodes, we will include the high-risk subset defined according to several risk factors based on our own retrospective data [29]. We choose DFS, rather than OS, as the primary endpoint, because the results of OS require longer follow-up and a larger patient population. Patients tend to survive longer after disease relapse because of the rapid development of effective salvage systemic therapy. Results from clinical trials will forever lag behind developments in clinical practice [11], which might not be applicable to patients treated in the future.

The value of IMNI for OS might be compromised by radiation-induced cardiac mortality, despite the DFS benefit. Cardiovascular toxicity is an important secondary endpoint in this study, which is assessed regularly by cardiologists to avoid an incomplete reporting of cardiac events [30]. IMNI will increase the heart dose [31] and has the potential to increase the risk of cardiac mortality, because there is a significant dose-effect relationship between acute coronary events or heart disease mortality and the mean heart dose [30]. In the protocol, the dose constraints to the heart and coronary arteries are required to be respected. Oncocardiology is an emerging field in cardiovascular and cancer healthcare [32]. We have developed an oncocardiology service for patients with breast cancer through close cooperation between cardiologists and oncologists. In this study, identification of baseline cardiac risk factors and early detection of radiation-induced cardiac damage, followed by adoption of preventive or therapeutic interventional strategies, might present the potential to reduce cardiac mortality.

Radiotherapy QA might affect clinical trial accrual, cost, outcomes, and generalizability, and is integral to this trial design. QA of non-CT-based IMNI in the DBCG study, using modern techniques to derive estimates of the doses to the IMN and OARs, showed that RT techniques utilizing electrons for IMNI had a high degree of IMN dose coverage with little variation in the patient population. However, in techniques using tangential fields for IMNI, estimates on IMN dose coverage were more uncertain, and some patients are likely to have received lower than the intended IMN dose [33]. A dummy run of the QA program in the Korean Radiation Oncology Group 08–06 Study, which is a phase 3 randomized trial designed to investigate the role of IMNI in breast cancer, revealed that various 3D RT techniques were adopted among participating institutions, and an average of 59.0% of the prescribed dose was delivered to the IMN in the no IMNI group, which was higher than expected because of the close proximity of the IMN to the medial margin of the chest [34]. According to our RT QA protocol, we will assess IMN delineation and evaluate the dosimetric parameters of the IMN and OARs. Careful data analysis and feedback will reduce inter-institutional heterogeneities and deviations from the protocol, which might help to provide reliable trial results.

## Conclusion

In conclusion, the POTENTIAL study is a pragmatic randomized trial that compares survival and toxicity outcomes of delivering IMNI with not delivering postmastectomy IMNI in patients with node positive breast cancer. We anticipate that the results of this trial will provide high-level type I evidence on IMNI that could improve the decision-making process.

## Data Availability

Data sharing is not applicable to this article as the current study is still open for inclusion of patients.

## Abbreviations

RT: radiotherapy
IMN: internal mammary node
IMNI: internal mammary node irradiation
3D: three-dimensional
DFS: disease-free survival
PMRT: postmastectomy radiation therapy
OS: overall survival
DBCG: Danish Breast Cancer Cooperative Group
CT: computed tomography
NCCN: National Comprehensive Cancer Network
RNI: regional nodal irradiation
LRR: locoregional recurrence
DM: distant metastasis
QoL: quality of life
ECOG: Eastern Cooperative Oncology Group
LVEF: left ventricular ejection fraction
PET: positron emission tomography
CTV: clinical target volume
PTV: planning target volume
IMRT: intensity-modulated RT
VMAT: volumetric modulated arc therapy
Dmax: maximum dose
OARs: organs at risk
EPID: electronic portal imaging device
CBCT: cone beam computed tomography
Dmean: mean dose
Vx: percent volume of the structure receiving x Gy
CTCAE 3.0: National Cancer Institute’s Common Terminology Criteria for Adverse Events version 3.0
RTOG: Radiation Therapy Oncology Group
EORTC: European Organization for Research and Treatment of Cancer
QA: quality assurance
